# Rationale and study design of the Adaptive study of IL-2 dose on regulatory T cells in type 1 diabetes (DILT1D): a non-randomised, open label, adaptive dose finding trial

**DOI:** 10.1136/bmjopen-2014-005559

**Published:** 2014-06-04

## Abstract

**Introduction:**

CD4 T regulatory cells (Tregs) are crucial for the maintenance of self-tolerance and are deficient in many common autoimmune diseases such as type 1 diabetes (T1D). Interleukin 2 (IL-2) plays a major role in the activation and function of Tregs and treatment with ultra-low dose (ULD) IL-2 could increase Treg function to potentially halt disease progression in T1D. However, prior to embarking on large phase II/III clinical trials it is critical to develop new strategies for determining the mechanism of action of ULD IL-2 in participants with T1D. In this mechanistic study we will combine a novel trial design with a clinical grade Treg assay to identify the best doses of ULD IL-2 to induce targeted increases in Tregs.

**Method and analysis:**

Adaptive study of IL-2 dose on regulatory T cells in type 1 diabetes (DILT1D) is a single centre non-randomised, single dose, open label, adaptive dose-finding trial. The primary objective of DILT1D is to identify the best doses of IL-2 to achieve a minimal or maximal Treg increase in participants with T1D (N=40). The design has an initial learning phase where pairs of participants are assigned to five preassigned doses followed by an interim analysis to determine the two Treg targets for the reminder of the trial. This will then be followed by an adaptive phase which is fully sequential with an interim analysis after each participant is observed to determine the choice of dose based on the optimality criterion to minimise the determinant of covariance of the estimated target doses. A dose determining committee will review all data available at the interim(s) and then provide decisions regarding the choice of dose to administer to subsequent participants.

**Ethics and dissemination:**

Ethical approval for the study was granted on 18 February 2013.

**Results:**

The results of this study will be reported through peer-reviewed journals, conference presentations and an internal organisational report.

**Trial registration numbers:**

NCT01827735, ISRCTN27852285, DRN767.

Strengths and limitations of this studyThis is an adaptive dose-finding trial that combines a new trial design with the use of immunological biomarkers to develop a new treatment for type 1 diabetes.The study incorporates detailed experimental medicine mechanistic studies that will investigate the actions of ultra-low dose IL-2 on the human immune system.The adaptive study design has required the development of new trial governance structures to allow data generated in the study to be rapidly analysed and utilised to inform dosing decisions.The study does not aim to determine the metabolic effects of treatment.

## Introduction

Type 1 diabetes (T1D) is the most common severe chronic autoimmune disease worldwide. The incidence of T1D is rising rapidly with a predicted increase in paediatric cases of 70% over the next 15 years in Europe.^1^ The aetiology of T1D is the autoimmune (loss of self-tolerance)-mediated destruction of insulin-producing pancreatic β cells leading to insulin deficiency and development of hyperglycaemia.^2^ At present, medical management of T1D focuses on intensive insulin replacement therapy to limit microvascular complications (retinopathy, nephropathy, neuropathy). Despite incremental improvement over the past 90 years clinical outcomes remain suboptimal with fewer than 5% of patients in the intensively treated group of the pivotal Diabetes Control and Complications Trial achieving glycaemic targets.^3^ The limiting factor for achieving euglycaemia was hypoglycaemia as a result of exogenous insulin treatment, that is, the tighter the glycaemic control the greater the frequency of hypoglycaemia.^4^ However, patients who had residual endogenous insulin function had a reduced level of microvascular complications and hypoglycaemia, which was most likely due to the preservation of the counter-regulatory responses to low blood sugars.^5^ These findings have led to intensive efforts to arrest the autoimmune process by novel immunotherapy and thereby preserve residual insulin production leading to improved clinical outcomes in T1D.

Genome-wide association studies have found that most genes contributing to T1D susceptibility encode proteins involved in immune regulation and immune function.^6^ In particular, several of the proteins are part of the interleukin 2 (IL-2) pathway that regulates T-cell activation and tolerance to self-antigens: IL-2, CD25, the α chain of the IL-2 receptor (*IL2RA*), *BACH2* and protein tyrosine phosphatase non-receptor type 2 (*PTPN2*).^7^ Phenotypic characterisation of CD25 expression on CD4 T-cell subsets has demonstrated that individuals carrying susceptibility alleles at *IL2RA* have memory CD4 T cells with reduced CD25 expression and less production of IL-2 on activation.^8^ Physiologically, IL-2 expression and signalling via the high-affinity trimeric IL-2 receptor is essential for the maintenance of self-tolerance and the prevention of autoimmunity.^9^

T regulatory cells (Tregs) and T effector (Teff) cells differ in their abilities to respond to IL-2 due to their distinct CD25 levels and the balance of their intracellular signalling molecules. In response to IL-2, Tregs intracellularly signal primarily via the pSTAT5 pathway while Teffs also activate the mitogen-activated protein kinase (MAPK) and PI3K/Akt pathways.^10^
^11^ Importantly, Tregs have a greater sensitivity to IL-2 due to their higher expression of the high-affinity IL-2 receptor compared with Teff cells. Natural Killer (NK) cells also require higher concentrations of IL-2 to be activated since this subset primarily expresses the intermediate affinity IL-2 receptor that is composed of dimers of the β and γ chains.^12^ The higher sensitivity of Tregs for IL-2 opens a therapeutic window where ultra-low doses (ULD) of IL-2 therapy can be used to enhance Treg responses in patients with T1D without increasing Teff or NK cells.

Aldesleukin or proleukin is a human recombinant IL-2 product produced by recombinant DNA technology using a genetically engineered *Escherichia coli* strain expressing an analogue of the human IL-2 gene. The in vitro biological activities of the native non-recombinant compound have been reproduced with aldesleukin.^13^ Aldesleukin is produced by Prometheus Laboratories on behalf of Novartis Vaccine and Diagnostics.

High-dose aldesleukin is currently indicated for the treatment of adults with metastatic renal cell cancer (RCC)^14^ and metastatic melanoma skin cancer.^15^ Initial clinical trials in metastatic RCC administered intravenously 600 000 IU/kg of aldesleukin every 8 hours days 1–5 days followed by 9 days of rest and further treatment on days 15–19. In responders repeat cycles are administered in 12 week intervals up to a total of 3 cycles. Less than 10% of patients had a complete response to IL-2 therapy.^16^ Alternative regimens with subcutaneous aldesleukin have also been used. Aldesleukin is administered at 18×10^6^ IU every day for 5 days, followed by 2 days of rest. For the following 3 weeks 18×10^6^ IU is administered on days 1 and 2 of each week followed by 9×10^6^ IU on days 3–5. On days 6 and 7 no drug is administered. After 1 week's rest this 4-week cycle is repeated.^16^ The reduced dose regimens, although minimising side effects, yield substantially lower clinical responses than the high-dose protocol and are not considered effective treatment of metastatic renal cell carcinoma.^17^

In patients with HIV, clinical trials of aldesleukin therapy have been conducted to determine whether increasing the CD4 T cell count would improve clinical outcomes (opportunistic disease or death from any cause). The Subcutaneous Recombinant Interleukin-2 in Patients with HIV with Low CD4 Counts under Active Antiretroviral Therapy (SILCAAT) trial administered a dose of 4.5×10^6^ IU twice daily for 5 days for six cycles with each cycle 8 weeks apart. The Evaluation of Subcutaneous Proleukin in a Randomised International Trial (ESPRIT) delivered 7.5×10^6^ IU twice daily for 5 days for three cycles with each cycle 8 weeks apart. In both trials aldesleukin induced an increase in CD4 cell count as compared with antiretroviral therapy alone. However, no additional clinical benefit was observed in the aldesleukin plus antiretroviral therapy groups. Neither the SILCAAT nor ESPRIT trial included a mechanistic analysis so it is unclear whether the aldesleukin therapy induced a population of Tregs that may have blunted the Teff function.^18^

A combination phase 1 trial of rapamycin and aldesleukin in recently diagnosed patients with T1D has been reported. The rationale for this combination originated from murine studies where rapamycin and IL-2 had been shown to prevent diabetes but not to reverse it in the non-obese diabetic mouse model.^19^ Additional data from other murine models suggested that rapamycin selectively inhibits Teff function as compared with Treg function.^20^ Rapamycin was administered at 2 mg/day for 7 days followed by a dose adjustment to achieve a serum level of 5–10 ng/mL for 12 weeks. Aldesleukin was started concurrently and administered subcutaneously at 4.5×10^6^ IU once a day for 3 days for four cycles. The combination treatment resulted in a transient decrease in pancreatic β function (as measured by C-peptide decline) that resolved after discontinuation of rapamycin. As preservation of residual insulin production in the pancreas is critical to improved clinical outcomes, further studies in patients with T1D should avoid combining rapamycin and IL-2.^21^

Two recent successful trials of low-dose aldesleukin in graft versus host disease (GVHD) and hepatitis C virus (HCV) induced vasculitis (VASCU-IL2) have been reported. Patients with chronic GVHD who were resistant to glucorticoid therapy were treated with either 0.3×10^6^, 1×10^6^ or 3×10^6^ IU/m^2^/day of aldesleukin for 8 weeks. The numbers of CD4 Tregs increased in all patients without an increase in Teff cells. Patients had sustained clinical responses with extended therapy and this enabled tapering of glucorticoids.^22^ HCV vasculitis patients were treated with 1.5×10^6^ IU once a day for 5 days followed by 3×10^6^ IU for 5 days for three cycles on weeks 3, 6 and 9. The proportion of Treg cells increased during treatment without an increase in Teff cells. Increased natural killer (NK) cells and eosinophilia were also noted with aldesleukin treatment. Overall, patients with HCV vasculitis, an autoimmune condition, demonstrated clinical improvement on this regimen.^23^

There is substantial non-clinical, preclinical and clinical data supporting the possibility that IL-2 (aldesleukin) therapy can arrest the autoimmune-mediated destruction of pancreatic β cells by induction of functional Tregs that inhibit islet-specific autoreactive Teffs. However, prior to embarking on large proof-of-concept trials in T1D it is essential that the optimal doses of IL-2 that induce increases in Treg functions are determined while simultaneously defining the cellular outcomes of treatment by detailed immunophenotypic, genetic and epigenetic analysis of peripheral blood cell subsets from participants before, during and after IL-2 in order to define mechanisms and biomarkers.

## Methods

### Study design

The DILT1D study is a 9-week, single centre non-randomised, single dose, open label, adaptive dose-finding trial. The study includes 12 visits: a screening visit, a treatment day, five visits to monitor the response to a dose of ULD IL-2, four visits to monitor the duration of response and a final follow-up visit on day 60 (figure 1). The DILT1D study has two phases: a learning phase and an adaptive phase. At the start of the study (learning phase) the first 10 participants will receive doses 0.04, 0.16, 0.6, 1, 1.5×10^6^ IU/m^2^ of IL-2, in ascending order with each of the doses being given to two patients before escalating the dose, and with at least a week between pairs of recruits. In the subsequent adaptive phase the data will be analysed sequentially after each participant is observed by fitting a candidate set of statistical models to the dose–response curve. Each model will provide an estimate and SE of the doses that achieve the two targets of a minimum Treg increase and a therapeutic Treg increase. Each model will also provide a recommended dose to assign to the next patient. The choice of doses will be approved by a dose determining committee (DDC) in the light of the reports and recommendations provided. The maximum dose of IL-2 that can be assigned is 1.5×10^6^ IU/m^2^. The study has been approved by Health Research Authority, National Research Ethics Service (13/EE/0020).

**Figure 1 BMJOPEN2014005559F1:**
[figure not shown]
Study design for the adaptive phase of dose on regulatory T cells in type 1 diabetes. The primary endpoint of the study is the maximum percentage increase in Tregs from baseline over the first 7 days following treatment with ultra-low dose interleukin 2 (IL-2). The T regulatory data from all participants treated are then used to inform the IL-2 dose administered to subsequent participants thereby more efficiently accessing the dose–outcome relationship.

### Dose determining committee

The scope of the DDC is to review the interim analysis after the first 10 trial participants and then provide decisions regarding the choice of dose to administer to subsequent participants. The DDC will also review all safety data accumulated in the trial at each meeting. The DDC will be comprised of a statistician, a physician and a scientist drawn from the members of the Trial Management Committee or named in the trial delegation log. More than one member from each role (statistician, physician and scientist) can attend the meeting but each role is only allowed a single vote at the DDC meeting. A statistician, a clinician and a scientist are required to attend to reach a quorate. Decisions at the DDC meeting can be reached by a majority vote. The Trial Steering Committee can be called on by the chair to review any decisions that cannot be agreed on if requested to by other member(s) of the DDC. Given the safety role of the DDC, the chair is the chief investigator or if unavailable, the chief investigator may delegate the chair to another physician.

After the 10th participant has completed 7 days of follow-up after administration of the drug, data will be extracted from the trial database and analysed. The interim analysis will be performed by the members of the Trial Management Committee and will be delivered to the DDC within 10 working days of this date for review. Following the interim analysis, data will be extracted from the trial database after each participant has completed 7 days of follow-up. A report generated from the data will be delivered to the DDC within one to two working days of this date, the tight timelines enabling the next dose to be prescribed for a patient treated at the start of the following week.

The report generated from the data by the trial statistician for the DDC to review will include: plots of all the patient profiles (Treg response vs time); plots of the sequence of doses; a scatter plot of the primary endpoint (maximal percentage change of Treg, log-transformed) versus dose; the same scatter plot of the primary endpoint versus dose with superimposed fitted models with 95% confidence bands for a list of statistical models; estimated target doses and CIs; residual plots of each model fitted; raw output from statistical packages to double-check on convergence and finally a choice of dose decisions for future patients. The statistical models will initially include: linear, quadratic, cubic, Emax, Emax4 (four parameter) and logistic (four parameter).

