### The DILT1D study outcome measures

The primary endpoint is based on the percentage of CD4 Treg (defined as CD3CD4CD25^high^CD127^low^) cells within the CD3 CD4 T-cell gate following treatment with IL-2 as measured by fluorescence-activated cell sorting (FACS). The maximum value observed in each patient's profile over the first 7 days of the follow-up period will be identified and the percentage change from the baseline value defines the primary endpoint.

The following secondary outcomes will be measured following IL-2 treatment:
Change in Treg number, phenotype and proliferation will be measured by FACS.Change in Treg cell epigenetic profile.Change in Teff number, proliferation and phenotype will be measured by FACS.Change in lymphocyte cell number, proliferation and phenotype subsets and NK and NKT cells will be measured by FACS and full blood count.Change in cytokines and soluble receptors.Change in metabolic control as measured by self-monitoring of blood glucose, laboratory measurement of blood glucose and glycated haemoglobin (HbA1c) and C-peptide.

The following exploratory endpoints will be measured:
Change in intracellular T and NK cell signalling will be measured ex vivo by FACS following IL-2 treatment. An in vitro dose–response to IL-2 will also be performed to assess durable changes in intracellular T-cell signalling.Change in Treg function will be measured by T-cell suppression assay.Change in T cell, NK and peripheral blood mononuclear cell gene expression.Participants will be characterised for genotypes at T1D susceptibility genes related to the IL-2 pathway.

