### Statistical methods

As an exploratory dose-finding study a formal sample size calculation is not appropriate. Simulation work shows that a sample size of 40 participants will give informative estimates of the target doses, assuming the underlying dose–response relationship can achieve the target responses within a safe range of doses and the between-patient variability does not dominate the dose–response relationship too much to be of practical clinical use.

A dose–response curve describing the relationship between the primary endpoint and the dose will be fitted for a selection of parametric models. Estimates and SEs for all parameters, including the interpatient variability, will be provided for all models, as well as an assessment of the goodness of fit for each model.^26^ An estimate, SE and 95% CIs will be produced for the doses associated with each of the different modelling assumptions that achieve the target response rates.

The target response rates are those that achieve a:
minimal Treg increase,maximal Treg increase.

However, the numerical values that define these increases will only be defined in the light of the data provided by the initial 10 participants. After analysis by the DDC and following review by the TSC these targets will be fixed for the course of the trial.

Summary statistics of all endpoints measured at baseline will be produced. Continuous variables will report sample size, mean, SD, median, minimum and maximum. Categorical or binary variables will report sample size, counts and percentages.

All secondary and exploratory endpoints measured after treatment will be explored using graphical methods, such as scatter plots, to examine their relationship to dose and other explanatory endpoints measured at baseline. A regression framework will be used to quantify such relationships, allowing for adjustments for baseline covariates and time point; transformations of the response variable will be made where appropriate and allowances for correlations within participants and/or within related endpoints will be made.

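### The dose-decision models are described as fitted to the log of a percentage change, a scale that is undefined without a rise and differs from the stated primary endpoint

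*Protocol article*

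**What the plan says.** The protocol article describes the primary endpoint in four places.

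- **The DILT1D study outcome measures.** The endpoint is built from each participant's peak, set against the pre-treatment value: "the percentage change from the baseline value defines the primary endpoint". No transformation is mentioned.
- **Figure 1 legend.** The endpoint is "the maximum percentage increase in Tregs from baseline over the first 7 days", again without a log.
- **Dose determining committee.** Each report contains "a scatter plot of the primary endpoint (maximal percentage change of Treg, log-transformed) versus dose", followed by "the same scatter plot of the primary endpoint versus dose with superimposed fitted models with 95% confidence bands". The models behind the dose recommendation are therefore shown on the logged endpoint.
- **Statistical methods.** "A dose–response curve describing the relationship between the primary endpoint and the dose will be fitted for a selection of parametric models". No scale is named. The one remark on transformation, "transformations of the response variable will be made where appropriate", stands in the paragraph on secondary and exploratory endpoints.

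The article gives no ratio form, no offset and no rule for a change of zero or below. The abstract says that doses in the adaptive phase are chosen to minimise the determinant of the covariance of the estimated target doses.

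**The concern.** A percentage change from baseline can be zero or negative, and then its logarithm does not exist. A small positive change gives a value far below the rest. Both are most likely at weak doses. Those doses matter here, because one of the two targets is the dose giving a minimal Treg increase and the Discussion says that a small rise is what the investigators want. Each of the five learning doses has only two participants, so one unusable value is half the data at that dose.

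The scale also determines what is estimated. A curve for the mean log percentage change, one for the mean percentage change and one for the mean log ratio are different curves, and one numerical target can correspond to a different dose on each. Once the adaptive phase starts, a report is due within one to two working days of each participant's 7-day data. A repair for an undefined value would then be chosen quickly, with the data in view, in an open-label trial.

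**Working it through.** The plan states no figure on this point, so there is none to reproduce. The checks below use the definitions above and some labelled assumptions.

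**1. The two transformations side by side.** Let R = 7-day maximum / baseline, so that percentage change = 100(R − 1).

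| R | % change | log(% change) | log R |
|---|---|---|---|
| 0.95 | −5 | undefined | −0.051 |
| 1.00 | 0 | undefined | 0 |
| 1.005 | 0.5 | −0.69 | 0.005 |
| 1.01 | 1 | 0 | 0.010 |
| 1.05 | 5 | 1.61 | 0.049 |
| 1.20 | 20 | 3.00 | 0.182 |

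Counting baseline towards the maximum would not help: negative changes would become exact zeros, which are still undefined.

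**2. How often the value is undefined.** Assumptions: k post-dose values in the 7-day window, exchangeable with baseline when the dose does nothing. Then P(maximum ≤ baseline) = 1/(k + 1). The Study design section lists five response visits but does not say that all fall within 7 days, so k = 5 is itself an assumption.

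- k = 5: 1/6 = 16.7% per participant; at least one of a pair, 1 − (5/6)² = 30.6%.
- k = 3: 25%. k = 7: 12.5%.

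With an effect the share falls. Simulating 400,000 profiles per setting, with lognormal within-person noise, five post-dose values and the rise at one visit only:

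| True peak rise | CV 5% | CV 10% | CV 15% |
|---|---|---|---|
| 10% | 5.3% | 11.4% | 13.3% |
| 20% | 0.4% | 5.8% | 9.6% |

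**3. Behaviour of the defined values.** Same simulation, assumed CV 10%, non-positive changes dropped:

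| True log rise | SD of log(% change) | SD of log R |
|---|---|---|
| 0 | 0.99 (skew −1.7) | 0.12 |
| 0.2, all five visits | 0.54 | 0.12 |
| 0.2, one visit | 0.82 | 0.13 |

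With all visits raised, the variance of log(% change) at no effect is (0.99/0.54)² ≈ 3.4 times that at the higher effect. The log ratio stays close to constant.

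**4. Direction of bias.** Back-transformed means at CV 10%, dropping non-positive changes for log(% change) and keeping everyone for log R:

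| True log rise | From log(% change) | From log R |
|---|---|---|
| 0 | 12.2% | 12.3% |
| 0.1, all visits | 21.2% | 24.1% |
| 0.1, one visit | 14.8% | 16.2% |

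Dropping participants without a rise pushes the mean up, and the near-zero positive values pull it down. At no effect the two roughly cancel; at the other settings the second dominates.

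**5. Effect of scale on a target.** If log(% change) were normal with an assumed SD of 0.5 to 1.0, the arithmetic mean would be exp(SD²/2) = 1.13 to 1.65 times the geometric mean. An arithmetic-mean target of 20% would then match a geometric mean of 20/1.13 = 17.7% down to 20/1.65 = 12.1%.

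**The case against.** The strongest reply is that the DDC phrase is a label in a list of report contents, not a formula. It may well be shorthand for the log of maximum over baseline, which is always defined. The Discussion says that Treg data from every enrolled participant will be used, which fits that reading. Defining an endpoint on its natural scale and modelling its log is ordinary practice, and the exact transformation may be in the analysis plan, which is not shown. The DDC also sees individual profiles, residual plots and raw convergence output, so a missing or extreme value would be noticed. Much of this stands: it lowers the severity. It does not remove the point, because the scale that the article states is the wrong one if the log ratio is meant, and an unsuitable one if it is not.

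Three stronger readings are tempting and are not supported.

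- **That the minimal-increase dose is biased downward.** This would need the low end of the curve to be raised. Step 4 shows it unchanged or lower when such participants are dropped, and an offset would keep them. The direction depends on handling that the article does not describe.
- **That the final models are on a different scale from the dosing models.** Statistical methods is silent on scale, and silence is not a statement that the data are untransformed.
- **That an undefined value among the first four participants is more likely than not.** The figure 1 − (5/6)⁴ = 52% requires no effect at both of the two lowest doses and five exchangeable visits, none of which is stated. The Discussion calls Tregs highly responsive at these doses.

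**Conclusion.** The point stands as a correction that is worth making, below the level of a flaw that must be fixed before the trial can proceed. The article names a modelling scale for dose decisions that conflicts with its own endpoint definition and, read literally, cannot be computed for a participant without a rise. Under the stated assumptions this affects up to about 1 in 6 participants at an ineffective dose (12.5% to 25% for seven to three values), and a smaller share as the effect grows. The defined values are skewed with a spread that changes with dose. Constant-variance standard errors, and the determinant criterion built on them, would then be distorted. That consequence holds only if the literal scale is used with constant variance. The visit count, CVs and effect sizes are assumptions, since the article gives none of them. If the log ratio was meant, what remains is a wording error that still needs correcting, because target doses depend on the scale.

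**What to change.** State the analysed endpoint once as log(maximum Treg % over the first 7 days / baseline Treg %). Use it for the DDC models and for the final dose–response models, in the Dose determining committee and Statistical methods sections. Keep percentage increase, as in the outcome section and the Figure 1 legend, as the back-transformed reporting scale. Convert both Treg targets to the log ratio when they are set after the first 10 participants; for example, an increase of 20% becomes log 1.20 = 0.182.

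The cost is one sentence of text and one line of code, with no new data. The trade-off is interpretive: fitted values become geometric-mean rather than arithmetic-mean increases, and the report should say so. The change should be in place before the first interim analysis.
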